### Assignment of interventions

The study will comprise two arms: one intervention group (parenteral nutrition group) and one control group (oral feeding group). The Zelen single-consent design requires that consent be obtained only from the intervention group, for their participation in a study involving initiation of parenteral nutrition. The patient will be informed of the study requirements (inclusion criteria, aims, composition, expected effects and benefits, foreseeable risks, contraindications and so on) to allow them to decide whether to consent to participate. The information delivered to the patient will not mention randomization. Patients allocated to the oral feeding group will be informed about their management, and will consent only to completion of the quality-of-life questionnaire. Patients randomized to the intervention group may refuse to consent to the intervention, in which case, they will be included in the control group.

The distribution of patients between the study arms will be performed by the investigator during the first consultation to verify eligibility criteria, by means of Internet access to a 1-to-1 randomization list, balanced by center, and generated automatically by using SAS software (version 9.3; SAS Institute Inc., Cary, NC, USA) and administered by the Clinical Investigation Centre of the University Hospital of Besancon, France.

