#### Sample size and recruitment

In a bilateral situation, a *P* value of <0.0166 will be considered clinically and statistically significant after Bonferroni adjustment for multiple testing, to ensure an overall bilateral alpha risk of 5%. To detect the minimal clinically significant difference (at least 10 points, with a standard deviation of 11 points), with a bilateral alpha risk of 0.0166 and a power of 80%, 54 patients per group are required. Interim analysis to evaluate the primary hypothesis is planned when half the patients have been included and have at least 2 months of follow-up. This interim analysis will be performed according to the rules established by O’Brien and Fleming (Alpha Spending Function with bounds calculated by O’Brien’s method) [24].

The calculation of the sample size takes into account the specificity of the randomization by the Zelen design, and the primary end point of quality of life measured with a multidomain questionnaire: Two groups of equal size, constituted by random assignment; one group will receive standard therapy, and the other group will receive the experimental therapy, or standard therapy if the patients refuses to consent to experimental therapy. The heterogeneity of the intervention group will increase the variance of the difference (Δ_z_) between groups for the primary end point, as compared with classic randomization (Δ_c_), albeit without introducing a measurement bias. The increase in variance will increase with the percentage (Φ) of subjects who receive standard treatment in the intervention group, with [25].

In these conditions, the number of subjects must be multiplied by (1/(1 - Φ)^2^). For the ALIM-K study, we estimate that the percentage (Φ) of subjects who receive standard treatment in the intervention group will be low (estimated at around 10% by experts). Quality of life, as measured by the questionnaire, will yield a score for each domain. To take into account the multiplicity of comparisons, the Bonferroni correction will be applied to the alpha risk.A variation in quality-of-life score of at least 10 points (on a scale of 0 to 100) will be considered as clinically significant.

At an alpha risk of 0.0166, power of 80%, and a percentage Φ of 10%, the number of subjects required to detect a difference of at least 10 points (±11) in quality-of-life score is at least 70 per group (54 × 1.25), or 140 patients in total.

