#### Primary objective

A treatment group will be considered as superior to the other if at least one of the three domains of the primary end point (physical function, overall health status/quality of life, or fatigue) of the QLQ-C15-PAL questionnaire is clinically and statistically significantly better, without any clinically and statistically significant deterioration in at least one of the other two domains.

Comparison of the three domains of the QLQ-C15-PAL questionnaire (between the parenteral nutrition and oral feeding groups) will be performed on an intention-to-treat basis for all patients randomized and included, by using ANOVA on scores at 2 months. Analyses will be adjusted for the presence (or not) of palliative chemotherapy. The variation in the score for each domain between inclusion (day 1) and day 60 will be compared with ANOVA, taking into account stratification variables and potential confounding factors, such as center, type of cancer, and patient characteristics.

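### The primary objective gives two ANOVAs per domain without saying which one decides, and neither conditions on the day-1 score; one baseline-adjusted model per domain would settle both at almost no cost

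*Protocol article*

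**What the plan says.** Under Primary objective, the three domains (physical function, global health/quality of life, fatigue) are compared between arms by intention to treat "by using ANOVA on scores at 2 months. Analyses will be adjusted for the presence (or not) of palliative chemotherapy". The next sentence gives a second analysis: "The variation in the score for each domain between inclusion (day 1) and day 60 will be compared with ANOVA". That second model allows for stratification variables, centre, tumour type and patient characteristics that are not listed. Neither analysis is called primary, supportive or sensitivity. The superiority rule at the start of the section needs one result per domain but names no model.

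Elsewhere in the article:

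- Outcomes defines the primary end point as quality of life evaluated at 2 months, or at discontinuation if earlier, and sets the clinically relevant difference at 10 points.
- Time schedule for participants (text and Table 2) has every patient complete the QLQ-C15-PAL on day 1.
- Assignment of interventions describes a "1-to-1 randomization list, balanced by center".
- Sample size and recruitment says that a p-value below 0.0166 "will be considered clinically and statistically significant after Bonferroni adjustment for multiple testing".

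**The concern.** Three things look weak.

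- **Which model decides is open.** A trial that claims superiority on at least one of three domains should have one p-value per domain. Here there are two candidates with different outcome variables and different covariates, and they can disagree. The article promises a statistical analysis plan only before database lock, yet plans an interim test of the primary hypothesis at half accrual, so the choice could still be open at that look.
- **The day-1 score is not a named covariate.** It is available for everyone and is likely to be a strong predictor of the 2-month score. The change score uses it by subtraction, which is efficient only when the correlation is high and does not fully remove chance baseline imbalance.
- **The 2-month ANOVA names no centre term**, although centre is the factor on which the list is balanced. The change-score ANOVA does include centre.

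At stake are precision, protection against chance imbalance, and protection against choosing the more favourable model.

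**Working it through.** **Inputs from the documents.** Three domains; two-sided alpha 0.0166 per domain; power 80%; "at least 10 points, with a standard deviation of 11 points"; 70 per group after inflation for an expected 10% refusal. **Assumed, not in the documents:** r, the correlation between day-1 and 2-month score, 0.3 to 0.7; between-domain correlation 0 to 0.7; equal SD at both times and the same r in both arms.

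**1. The plan's alpha.** 3 × 0.0166 = 0.0498; if the tests were independent, 1 − (1 − 0.0166)³ = 0.0490. The three-domain split is correct.

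**2. If a win on either ANOVA counted.** 6 × 0.0166 = 0.0996; if independent, 1 − (1 − 0.0166)⁶ = 0.0956. The two tests of one domain are correlated at √((1 − r)/2), which is 0.59, 0.50 and 0.39 for r of 0.3, 0.5 and 0.7. Simulation under no effect (2,000,000 draws, any rejection in either direction, no 10-point criterion and no veto for deterioration) gives:

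| Between-domain correlation | Three tests | Either ANOVA, r = 0.3 / 0.5 / 0.7 |
|---|---|---|
| 0 | 4.9% | 8.9 / 9.1 / 9.3% |
| 0.5 | 4.4% | 8.0 / 8.2 / 8.4% |
| 0.7 | 3.9% | 7.0 / 7.2 / 7.4% |

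**3. The 10-point criterion.** With SD 11 and 70 per group, the standard error of the difference in 2-month scores is 11 × √(2/70) = 1.86. The 0.0166 threshold is 2.395 × 1.86 ≈ 4.5 points, and 10 points is 10/1.86 ≈ 5.4 standard errors. If an observed difference of 10 points is also required, the summed error over all six tests is below 0.002%. This depends on the SD: at SD 25 the threshold is 2.395 × 25 × √(2/70) ≈ 10.1 points, so the criterion would add almost nothing.

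**4. Precision.** Residual variance relative to the 2-month score is 1 for the score ANOVA, 2(1 − r) for the change score and 1 − r² with the day-1 score as covariate. The last column uses n = 2 × SD² × (z₁₋α/₂ + z₀.₈)² / 10², normal approximation, with SD² = 121 multiplied by each relative variance.

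| r | Score | Change | Baseline-adjusted | n per group (score / change / adjusted) |
|---|---|---|---|---|
| 0.3 | 1 | 1.40 | 0.91 | 26 / 36 / 24 |
| 0.5 | 1 | 1.00 | 0.75 | 26 / 26 / 20 |
| 0.7 | 1 | 0.60 | 0.51 | 26 / 16 / 13 |

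The adjusted model needs 9%, 25% or 49% fewer patients than the score ANOVA, and 35%, 25% or 15% fewer than the change-score ANOVA.

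**5. Power already available.** Refusal of 10% dilutes a 10-point effect to 9. With 70 per group, 9/1.86 − 2.395 ≈ 2.45, which is about 99% power for the plain score ANOVA.

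The article states "with a bilateral alpha risk of 0.0166 and a power of 80%, 54 patients per group are required". The same inputs give 26 per group (27 by the t-test), so 54 matches the total for two groups. That is a separate matter, and this point does not rest on it.

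**The case against.** The strongest reply is that the deciding model can be inferred. The end point is defined at 2 months, the first ANOVA matches that definition, and the change-score sentence with its broader covariates reads naturally as support. This largely stands. A reader might infer that the plan runs six tests against an alpha meant for three, but nowhere does the article say that either ANOVA may establish superiority. What remains is that the change-score ANOVA sits under the primary heading without a label. Sample size and recruitment also expresses the clinical criterion as a variation in score, the word used for the change-score analysis.

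Second, superiority must be clinical as well as statistical, so error rates based on p-values alone do not describe the written rule. This stands under the stated SD, as step 3 shows. It is weaker if the SD is larger, and the sentence that treats p below 0.0166 as clinically as well as statistically significant leaves the criterion less firm than it should be.

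Third, a reader might infer that the trial loses needed power, that baseline is ignored altogether, or that centre is left out. None of these is supported. Power is about 99% on the plan's own inputs, the change score uses baseline by subtraction, and centre is absent only from the first model. Omitting a balancing factor tends to make standard errors too large, which is conservative, and its size cannot be computed from the documents.

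Fourth, exact covariate lists are commonly left to the analysis plan, and an ANOVA on randomised follow-up scores is valid. Both are true. But the article does not defer the model; it states two under the primary objective and ranks neither. The case for baseline adjustment is one of efficiency, not of error.

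**Conclusion.** The point holds in a limited form. Two ANOVAs per domain stand under the primary objective, the deciding one is not named, neither conditions on the day-1 score, and the 2-month ANOVA names no centre term. On the most natural reading the alpha is kept at 0.0498. The 7 to 9% figure applies only if either model may decide on its p-value alone, and it rests on assumed correlations.

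A single baseline-adjusted model is at least as precise as either stated analysis, apart from one degree of freedom. The gain depends on r: a residual variance of 0.51 to 0.91 of that of the 2-month score for r from 0.7 down to 0.3. Under the stated SD of 11 this is a free improvement in precision and in protection against chance imbalance and selective choice of model, not a demonstrated loss of power or alpha. It would matter more if the SD proves larger or if many 2-month scores are missing.

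One caveat: day 1 falls after allocation in this design, so using the day-1 score assumes that knowing the allocation has not shifted it. The planned change-score analysis makes the same assumption.

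**What to change.** Under Primary objective, name one primary model per domain: the 2-month score as defined under Outcomes, on allocated arm, the day-1 score of the same domain, centre (as a random effect, or with small centres pooled) and palliative chemotherapy status fixed at day 1, tested at 0.0166. State that the superiority rule, including its veto for deterioration, uses the estimate and p-value from this model and no other, and that the 10-point criterion is required in addition to the p-value. Label the change-score ANOVA, and any model with tumour type or further patient characteristics, as supportive with no role in the decision.

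Make the change in the protocol and the analysis plan before the interim analysis. It costs wording only: the day-1 questionnaire, centre and ongoing treatment are already recorded, and neither the sample size nor the alpha has to change.

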#### Change in quality of life over time

Quality-of-life scores will be generated according to algorithms described in the EORTC scoring manual. The mechanism of missing scores will be studied and classified according to the methods of Diggle [26] and Rubin [27] (that is, MCAR (Missing Completely At Random), MAR (Missing At Random), and MNAR (Missing Not At Random). The mechanism of missing data will be determined by comparing patients with no missing scores with those with at least one missing score at baseline, according to baseline characteristics of patients. If required, more detailed patterns will be defined. If missing data are MNAR, multiple imputations may be performed. Otherwise, simple imputation by the mean will be retained.

The time to quality-of-life score deterioration (TTD) will be defined as a modality of longitudinal quality-of-life analysis and will be defined as the time from inclusion in the study to a first deterioration, with a minimum clinically significant difference of at least 5 points as compared with the baseline score, or death of any cause, whichever occurs first [28, 29]. Although three domains of the EORTC QLQ-C15-PAL are being targeted for the primary end point, scores from all domains of the questionnaire will be studied as secondary analyses. The TTD curves will be calculated by using the Kaplan-Meier method and described, by using median and 95% confidence interval (CI). TTD curves will be compared according to treatment group by using the log-rank test and univariate Hazard Ratio with 95% CI. A multivariate Cox regression model will then be performed to investigate potential prognostic factors of TTD. All variables collected at baseline will be tested by univariate analysis. Variables with a *P* value ≤0.20 by univariate analysis will be eligible for inclusion in the multivariate Cox analysis.

Mixed-model analyses of variance for repeated measures will also be performed to test a time effect, a treatment effect, and an interaction between time and treatment. If missing data are not completely at random, a pattern-mixture model will be used.

Analysis of the secondary end points will focus first on comparison of overall survival. Overall survival is defined as the time from study registration to death of any cause. Patients who are lost to follow-up will be counted at the date of their last follow-up.

For all time-to-event end points, the 95% CI of the median survival will be calculated with the Brookmeyer and Crowley method [30]. The two treatment arms will be compared with the log-rank test.

Hazard ratios with 95% CI will be estimated by using Cox’s univariate proportional hazards model. Follow-up will be estimated by using reverse Kaplan estimation.

A multivariate Cox regression model will be performed to investigate potential prognostic factors. All variables collected at baseline will be tested in univariate analysis. Variables with an univariate *P* value ≤0.20 will be eligible for multivariate Cox analysis. A bootstrap procedure will be used to check internal validation of the model. The discriminatory capacity of the model will be assessed with Harrell C statistic. Reclassification ability will be examined with Net Reclassification Improvement (NRI) [31] and Integrated Discrimination Improvement (IDI) [32].

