#### Outcomes

**Primary outcome** The primary end point is health-related quality of life specific to the palliative phase of cancer, evaluated at 2 months (or at treatment discontinuation for patients who discontinue treatment allocation before 2 months), by using the European Organisation for Research and Treatment of Cancer (EORTC) Quality of Life Questionnaire Core 15 Palliative (QLQ-C15-PAL), in particular, the physical function, global health, and fatigue subscales [13].

The QLQ-C15-PAL will be proposed to the patient at inclusion in the study, and at every follow-up visit until death. If necessary, help is available for patients to complete the questionnaire (reading out the questions, explaining the different response options, taking any notes). The QLQ-C15-PAL is the short version of the QLQ-C30 adapted for patients in palliative care [13]. The 15 items are divided into two functional subscales (physical function, three items; and emotional function, two items); two symptom subscales (fatigue, two items; and pain, two items); five single items (dyspnea, appetite loss, sleeping disorders, constipation, and nausea/vomiting), and one item evaluating global health status/quality of life. Linear transformation of the item responses yields a score for each subscale (or single items) ranging from 0 to 100. A higher score corresponds to a higher level of global quality of life and functional aspects, and a greater level of symptoms on the symptom scale. The subscales physical function, global health status/quality of life, and fatigue will be evaluated for the primary end point. The minimum clinically significant difference is fixed at 10 points [21].

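### The missing-score rule is reversed: multiple imputation is optional and kept for MNAR, mean imputation is fixed for MCAR and MAR, and the test that chooses between them cannot identify MNAR

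*Protocol article*

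**What the plan says.** All references are to the protocol article.

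- *Change in quality of life over time* classifies missing scores as MCAR, MAR or MNAR and then fixes the consequence: "If missing data are MNAR, multiple imputations may be performed. Otherwise, simple imputation by the mean will be retained".
- The classification is made by "comparing patients with no missing scores with those with at least one missing score at baseline, according to baseline characteristics of patients". The section adds that finer patterns may be defined if needed.
- Later in the same section, for the repeated-measures mixed model: "If missing data are not completely at random, a pattern-mixture model will be used".
- *Primary objective* compares the three domains "on an intention-to-treat basis for all patients randomized and included, by using ANOVA on scores at 2 months". It names no method for missing scores.
- *Outcomes* defines the primary score as "evaluated at 2 months (or at treatment discontinuation for patients who discontinue treatment allocation before 2 months".
- Time to deterioration counts a first deterioration "or death of any cause, whichever occurs first". The imputation rule does not mention death.

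**The concern.** Three things are wrong with the rule as stated.

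**The allocation is backwards.** The second branch covers both MCAR and MAR. MAR is the setting in which multiple imputation works, yet there the plan fixes a single mean. Under MNAR, where standard multiple imputation is not by itself a remedy, the plan offers it, and only as an option.

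**The gate cannot do its job.** A difference in baseline characteristics between patients with and without missing scores is evidence against MCAR. Whether the data are MAR or MNAR depends on the unseen scores, which baseline data cannot reveal. MNAR can therefore never be established this way, and the mean-imputation branch becomes the default.

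**MAR data are treated in two ways.** The imputation rule sends them to a mean. The mixed-model rule sends them, as data that are not MCAR, to a pattern-mixture model.

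At stake is the primary comparison. Patients at the palliative stage, assessed at 2 months, can be expected to miss questionnaires. Superiority requires a difference that is both statistically significant (P < 0.0166) and clinically significant (10 points), so both the standard error and the size of the estimate matter.

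**Working it through.** The plan gives no operating figure for this rule, so there is none to reproduce.

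**Inputs from the article.** N = 70 per group; two-sided alpha 0.0166 per domain; difference 10 points; SD 11 (*Sample size and recruitment*). The 54 per group stated there before inflation is not used.

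**Assumptions.** The missing fraction m is the same in both arms and ranges over 10% to 40%; data are MCAR unless stated; the rule applies to the 2-month comparison.

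**1. Arm-mean imputation.** Let n = N(1 − m) be the observed number per arm. Each imputed value equals its arm mean, so the mean difference and the residual sum of squares (SS) do not change. Only the counts do.

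- Variance that is reported: SS/(2N − 2) × 2/N
- Variance that is justified: SS/(2n − 2) × 2/n
- The t statistic is therefore too large by f = √[(N/n) × (2N − 2)/(2n − 2)], which is roughly 1/(1 − m).

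The critical value is 2.425 (138 df). The actual type I error is 2 × P(T > 2.425/f) with 2n − 2 df.

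| m | n | f | 2.425/f | Type I error | Multiple of 0.0166 |
|---|---|---|---|---|---|
| 10% | 63 | 1.112 | 2.181 | 3.1% | 1.9 |
| 20% | 56 | 1.252 | 1.937 | 5.5% | 3.3 |
| 30% | 49 | 1.433 | 1.692 | 9.4% | 5.7 |
| 40% | 42 | 1.675 | 1.448 | 15.1% | 9.1 |

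Simulation (20,000 runs) gave 5.8%, 9.8% and 15.4% at 20%, 30% and 40%.

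**2. Overall-mean imputation.** Both arms receive the same constant for a fraction m of patients, so the expected difference is (1 − m) × 10.

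| m | Expected estimate | Simulated estimate | Simulated type I error |
|---|---|---|---|
| 10% | 9 | – | – |
| 20% | 8 | 7.98 | 1.7% |
| 30% | 7 | 6.99 | 1.6% |
| 40% | 6 | 5.97 | 1.7% |

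Power to reach P < 0.0166 is almost that of the observed cases (95.3% against 95.4% at 40% missing). The damage is to the estimate.

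**3. MAR check.** Scores were made more often missing at low baseline, equally in both arms, with an assumed baseline-to-follow-up correlation of 0.5. There were 3,000 runs under the null and 1,000 under a 10-point effect.

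| Method | Type I error, 23% / 41% missing | Estimate of 10 points, 23% / 41% missing |
|---|---|---|
| Arm mean | 7.3% / 16.5% | 9.97 / 9.99 |
| Overall mean | 1.9% / 1.6% | 7.7 / 5.9 |
| Multiple imputation (arm, baseline score) | 2.0% / 1.7% | 9.94 / 9.95 |

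The arm-mean estimate is unbiased here only because missingness was made symmetric between arms. The Monte Carlo standard error of a type I rate near nominal is about 0.23 percentage points. Multiple imputation, in the setting where the plan withholds it, restores both properties.

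**The case against.** The reversal itself has no good defence, and a later SAP does not cure it: the article commits to a rule rather than leaving the matter open. The stronger objections concern reach and size.

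- **Scope.** The rule is placed with the longitudinal analysis, and *Primary objective* does not mention imputation. This stands as a caveat. Applying the rule to the 2-month ANOVA is an inference from its general wording and from the absence of any other rule.
- **Magnitude.** No missing fraction is given and the mean is not identified; a patient's own mean would behave differently from either case above. Severalfold inflation needs the arm mean and about 20% missing or more; at 10% it is 1.9-fold. This stands.
- **The 10-point threshold.** With a true difference of exactly 10, about half of estimates from complete data would fall below 10 anyway. The attenuation is real, but it should not be read as turning certain success into failure.
- **Death.** A reader might infer that the plan assigns average scores to patients who died and so hides a mortality effect. The article does not say this. The primary score may be taken at treatment discontinuation, questionnaires continue until death, and the SAP may treat death separately. A survival difference would also show in overall survival and in time to deterioration. What remains is narrower: read literally, the rule makes no exception for a patient who dies with neither a 2-month nor a discontinuation score.
- **Pattern-mixture trigger.** One might call this the same mistake. It is not. Using such a model for MAR data is more cautious than necessary, not invalid. The defect is only its inconsistency with the imputation rule.
- **Baseline wording.** One might read "The mechanism of missing data will be determined by comparing patients with no missing scores with those with at least one missing score at baseline" as confining the check to scores missing at baseline. The sentence is ambiguous and finer patterns are allowed for, so the point does not rest on that reading.

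**Conclusion.** The concern holds for the rule and its gate. The plan fixes mean imputation where it is not valid, makes multiple imputation optional where it is not sufficient, and chooses between them with a comparison that cannot identify MNAR. None of that depends on an assumption.

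The numerical consequence is conditional on the rule governing the primary ANOVA and on the assumed 10% to 40% missing. Under arm-mean imputation, per-domain type I error is then about 3.1% to 15.1% against 1.66%. Under overall-mean imputation, type I error is about nominal but a true 10 points is estimated as about 9 down to 6. Either the test or the estimate is damaged, and the article does not say which. No claim is made that deaths are hidden or that the mixed-model plan is invalid.

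**What to change.** 1. Delete mean imputation, and stop using the mechanism test to choose the method. The comparison of patients with and without missing scores can stay as description.
2. Name one MAR-valid method for the 2-month comparison: either the repeated-measures mixed model already planned, or multiple imputation using arm, baseline and earlier scores, and palliative chemotherapy. Questionnaires are planned at least monthly, so earlier scores should exist for many patients.
3. Keep the pattern-mixture model, or a delta-adjusted analysis, as an MNAR sensitivity analysis that is run whatever the baseline comparison shows.
4. State that scores after death are not mean-imputed, and report deaths before day 60 by arm.
5. Say explicitly that these rules apply to the primary ANOVA as well as to the longitudinal analyses.

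The SAP is due before database lock, so this is a change of wording with slightly more programming. Confidence intervals will be wider than under mean imputation, and correctly so.

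### Quality-of-life scores judged MCAR or MAR are to be filled by a single mean, while multiple imputation, valid under those mechanisms, is only an option for MNAR

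*Protocol article*

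**What the plan says.** The rule is in the Statistical analysis part of the protocol article, under Change in quality of life over time. Missing scores are to be classified as MCAR, MAR or MNAR by "comparing patients with no missing scores with those with at least one missing score at baseline, according to baseline characteristics of patients". Two sentences then fix the handling: "If missing data are MNAR, multiple imputations may be performed", followed by "Otherwise, simple imputation by the mean will be retained". The first is permissive and the second is a commitment. With three mechanisms listed, the second covers MCAR and MAR. Whether the mean is that of the arm, of all patients or of the patient's own scores is not stated.

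Later in the same section, in the paragraph on the repeated-measures mixed model, a further rule appears: "If missing data are not completely at random, a pattern-mixture model will be used".

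The primary comparison is described separately, under Primary objective. It is made "on an intention-to-treat basis for all patients randomized and included", "by using ANOVA on scores at 2 months". That section has no rule for missing scores. To count in a group's favour, a domain must be one that "is clinically and statistically significantly better".

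**The concern.** Single mean imputation treats filled-in values as if they had been observed. It understates the residual variance, overstates the sample size and, under MAR, ignores the baseline variables that predict missingness. Standard multiple imputation addresses these problems under MCAR and MAR, where the plan does not use it. Under MNAR it needs an explicit departure, such as a delta shift, and the article mentions none.

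Quality of life is the primary endpoint, read at 2 months in palliative patients whose required life expectancy is just over 2 months, so a material number of missing scores is foreseeable. The rule matters even if it is confined to its own section. In the mixed model it distorts the variance. In the time-to-deterioration analysis, an imputed mean set against a patient's own baseline can create or hide a 5-point event.

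**Working it through.** **Inputs.** From Sample size and recruitment: 70 patients per group, SD 11 points, two-sided alpha 0.0166 per domain (critical value 2.395), clinically significant difference 10 points. The article gives no missing-score rate, so m = 10% to 40% is an assumption. It also gives no figure of its own on this point to reproduce.

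**Arm mean, MCAR, same m in both arms.** The point estimate equals the complete-case difference.

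- True SE = SD × √(2 / (n(1−m)))
- Reported SE ≈ SD × √(1−m) × √(2/n), because the filled-in values add nothing to the sum of squares while n is counted in full
- Ratio of reported to true SE = 1−m
- Error rate of the P value = 2 × (1 − Φ(2.395 × (1−m)))

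At m = 20%: 2.395 × 0.8 = 1.916, giving 5.5%.

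**Overall mean, MCAR, same m in both arms.** Both arms receive the same value for the missing fraction, so the expected difference is multiplied by (1−m). The SE of the estimate shrinks by the same factor.

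| Missing m (assumed) | Reported/true SE, arm mean | Error rate of nominal 1.66%, arm mean | Simulated | True 10 points becomes, overall mean |
|---|---|---|---|---|
| 10% | 0.90 | 3.1% | 3.0% | 9 |
| 20% | 0.80 | 5.5% | 5.4% | 8 |
| 30% | 0.70 | 9.4% | 9.4% | 7 |
| 40% | 0.60 | 15.1% | 15.4% | 6 |

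The simulation used 20,000 trials per row (70 per group, SD 11, t-test at 0.0166). Over the same rows, complete-case analysis and overall-mean imputation both rejected in 1.6% to 1.7% of null trials. Complete-case analysis kept the 10-point effect.

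**MAR illustration (all settings assumed).** There is no true effect and the baseline correlation is 0.6. In one arm, patients with poorer baseline scores are more often missing (35% overall); in the other, 30% are missing at random. Over 4,000 trials, arm-mean imputation gave an average difference of −2.5 points and rejected in 32%. A baseline-adjusted analysis of the observed scores, standing in for a likelihood model or multiple imputation, gave −0.02 points and rejected in 1.4%. A milder setting (20% against 35–50% missing) gave a bias of 0.8 to 1.6 points.

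**What the 10-point condition does to the arm-mean inflation.** The true SE at 20%, 30% and 40% missing is 11 × √(2/56) = 2.08, 11 × √(2/49) = 2.22 and 11 × √(2/42) = 2.40. Under the null, the chance of an observed difference of 10 points or more in either direction is about 1.5 in a million, 7 in a million and 3 in 100,000. With an assumed SD of 20 and 40% missing, the SE is 20 × √(2/42) = 4.36 and the chance is about 2.2%.

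**The two rules side by side.** Not MCAR means MAR or MNAR. So under MAR the section calls both for mean-imputed scores and for a pattern-mixture model, without saying which analysis each one serves.

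**The case against.** **The rule is in the longitudinal section, and those analyses are secondary.** This stands. Primary objective contains no imputation instruction. A reader might infer that the article orders mean imputation for the primary ANOVA, but it does not say so. The inference is likely, because an intention-to-treat comparison of all patients randomized and included needs some rule for missing scores and no other imputation rule is given. It remains an inference.

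**The superiority decision also requires clinical significance.** This stands too. A reader might take 15% as the chance of wrongly declaring one group superior. At SD 11 the 10-point condition makes that very rare, as shown above. The protection is not complete: it weakens with a larger SD, and one sentence in Sample size and recruitment attaches clinical as well as statistical significance to P < 0.0166 alone.

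**It is not the only missing-data rule, and the plan limits missingness at source.** The pattern-mixture sentence is a second rule. Moving the assessment to treatment discontinuation for early stoppers, and offering help with the questionnaire, should reduce missing scores. The missing rates used here are therefore assumptions.

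**The two rules under MAR need not contradict each other.** The pattern-mixture sentence belongs to the mixed model, imputation could serve other analyses, and original missingness indicators could still define patterns. So this is an unreconciled overlap, not a proven contradiction.

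**The sentence may mean item-level or baseline-only imputation, or the SAP may replace it.** These readings do not remove the problem. Scoring by the EORTC manual is stated separately, and the sentence follows a classification of missing scores. The mention of baseline describes the comparison used to judge the mechanism; the imputation sentence is not limited to baseline scores. A later SAP could change the rule, but the protocol commits to it as written.

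**Conclusion.** The concern holds as a wrongly fixed imputation rule. Single mean imputation does not in general give valid inference under MCAR, MAR or MNAR. It would be too neat to say that the plan simply swaps two methods, since mean imputation would not suit MNAR either. The plan withholds multiple imputation where its standard form is valid, and offers it without a stated departure where one is needed. That offer does not rule out a shifted version.

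The two harms are alternatives, and the unstated choice of mean decides between them. The arm mean gives error rates of about 3% to 15% for a nominal 1.66% P value at 10% to 40% missing. The overall mean keeps the type I error but pulls a true 10-point difference below the protocol's own threshold, to 8 points at 20% missing and 7 at 30%. These figures assume MCAR and equal missingness in both arms. Their size depends on the assumed rates; the direction under each choice of mean does not. They describe the P value and the estimate, not the probability of a false claim of superiority.

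**What to change.** Delete the mean-imputation sentence and put in its place:

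- Under MCAR or MAR, analyse the observed scores with the likelihood-based mixed model already planned. Alternatively, use multiple imputation by arm, including baseline score, palliative chemotherapy, performance status and interim scores, combined by Rubin's rules.
- Keep the pattern-mixture model, or delta-adjusted multiple imputation, as a pre-planned sensitivity analysis for MNAR. This also resolves the overlap under MAR.
- State which analyses the rule governs, including the 2-month ANOVA.

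The cost is two or three sentences in the protocol or SAP, settled before database lock, and standard software. No extra data are needed. If the arm mean was intended, P values will become less favourable.
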